## Abstract

**Background:**

In this paper, we present the protocol for a cluster randomised controlled trial to evaluate the effectiveness and implementation of a participative risk management intervention to address work-related musculoskeletal disorders (WMSDs). The aims of the study include to evaluate the implementation process and the impact of the intervention on work related musculoskeletal pain and discomfort and exposure to physical and psychosocial hazards in paramedics over a 12-month period.

**Methods:**

The intervention in this study is to implement A Participative Hazard Identification and Risk Management (APHIRM) toolkit in an ambulance service. Eighteen work groups containing eligible participants (registered paramedics) will be randomised into the intervention or wait-list control arm in one of three rolling recruitment periods. The APHIRM toolkit survey will be offered at baseline and 12 months later, to all current eligible participants in each work group allocated to the trial. The intervention work groups will receive the remainder of the APHIRM toolkit procedures. Identifying data about individual participants will not be collected in the survey, to protect participant privacy and encourage participation. Changes in primary (musculoskeletal pain and discomfort) and secondary (exposure to physical and psychosocial hazards at work) outcomes measured in the survey will be analysed comparing the baseline and follow up response of the cluster. A process evaluation is included to analyse the implementation and associated barriers or facilitators.

**Discussion:**

This study is important in providing a comprehensive approach which focusses on both physical and psychosocial hazards using worker participation, to address WMSDs, a well-known and significant problem for ambulance services. The effectiveness of the intervention in work groups will be rigorously evaluated. If significant positive results are observed, the intervention may be adopted in ambulance services, both nationally and internationally.

**Trial registration:**

ISRCTN77150219. Registered 21 November 2021.

**Supplementary Information:**

The online version contains supplementary material available at 10.1186/s12891-023-06834-8.

## Background

Musculoskeletal disorders are a common and costly health condition affecting 1.71 billion people globally in 2019 [1] which includes workers [2–4]. In Australia, work-related musculoskeletal disorders (WMSDs) have been identified as a leading work health and safety (WHS) problem in terms of frequency and costs, exceeding $24 billion AUD in 2012–13 [5]. Pain and discomfort can be experienced by an individual with a musculoskeletal condition, along with general health problems, anxiety, disturbed sleep and reduced mental wellbeing [3, 6–8], with impacts on absenteeism and disability [9–11]. If work participation is reduced through chronic musculoskeletal conditions such as arthritis or back problems, the cost to the individual and society is significant [12, 13] and this is exacerbated for individuals with other chronic conditions [14]. An extensive evidence base supports the complex aetiology of WMSDs, involving psychosocial, physical and organisational factors [5, 15–17]. However, there is evidence that proactive workplace risk management of psychosocial hazards is not routinely undertaken [18], despite the importance of these in the development of WMSD being highlighted [19–21]. Failure to translate evidence about WMSD risk management into practice was also identified as a gap when Australian organisations undertook investigations related to WMSDs, as a strategy to learn and prevent future incidents [22]. Substantial practical challenges exist in developing, implementing, and measuring workplace interventions to address WMSDs [5], which may explain the current situation.

WMSDs are a major occupational health problem for the healthcare and social assistance workforce [23–28]. In Australia, 8.6 serious claims for workers’ compensation were reported per million hours worked in 2019–20 in the industry [4]. In 2021 there were more than 22,000 paramedics registered in Australia, with approximately equal numbers of males and females, and the majority under 40 years of age [29]. Frontline workers who perform ambulance service work have high exposure to risk factors for WMSD and a high prevalence of adverse musculoskeletal health outcomes related to their work [20, 30–32]. Ambulance officers in Victoria, Australia were 13 times more likely to have a low back workers’ compensation claim compared to nurses during the period 2009—2012 [33]. The critical role of frontline ambulance personnel during the COVID-19 global pandemic and the increasing demand on support services to support their mental health and wellbeing has been recognised [34]. A survey of Australian paramedics about the impact of the COVID-19 pandemic found significant reporting of symptoms of burnout, anxiety and other mental health conditions along with perceived lack of organisational support [35]. Despite the significance of this workforce in the healthcare system and the known problem of exposure to WMSDs, limited research has been undertaken to assess and intervene in the design of work to optimise the musculoskeletal health of ambulance personnel, taking into account the work system within which they operate [30]. Previous research has largely focussed on specific aspects of the role, including stretcher design [31], loading technique [36], paramedic bags [37] and evaluating ambulance patient compartments [38].

WMSDs are complex, outlined in a model by Macdonald and Oakman [17] which refers to three important groups of work-related factors (physical, psychosocial and organisational), and that a poor match between these and individual factors, could lead to hazardous within person effects (high biomechanical load, fatigue, stress response) and increased risk of WMSD in the individual, who may experience discomfort, pain and/or tissue damage [10, 21, 28]. Given this complexity, interventions need to be multilevel and target multiple hazards using principles of systems thinking and implementation science [17, 20]. A multifaceted approach to workplace interventions which addresses tasks, equipment, training, and policy, has been identified as effective in the healthcare and community sector [24, 26, 28] and specifically in patient handling interventions in healthcare settings [25, 39], which were found to be in common use in Australian workplaces [40]. Participatory ergonomics (PE) processes have been identified as important in WMSD prevention [41–43], including in the healthcare sector [42]. A PE intervention has been described as one where workers or end users are involved in the process [44]. The Participatory Ergonomics Framework (PEF) provides a validated set of nine dimensions, with categories to describe the nature of the dimension in a particular intervention and guide the description of PE in practice [45]. Describing PE interventions along with the outcomes they achieve is important, as by the very nature of being participatory they are heterogenous, varying in intensity and implementation process [41, 44]. However, one review identified that many PE studies did not use the PEF to describe the intervention, making comparison of results between studies difficult [41]. A review [44] identified several important factors for successful PE interventions including the right people being involved; addressing barriers/facilitators; defining responsibilities; providing ergonomic training and making decisions using group consultation. Barriers to effective WMSD interventions include failure to adopt a systems approach to risk management; inadequate risk controls; lack of attention to commitment, culture, climate or worker participation; degree of competency to intervene and legislation [5]. Psychosocial factors in the workplace can impact the success of a participative intervention and may be influenced by the intervention itself [6, 43]. For example, poor relationships between workers and managers may hinder the implementation of PE, but a successful PE process may improve the relationships as the PE intervention proceeds over time, providing direct benefits within and indirect benefits beyond the PE process.

This paper details the protocol for a cluster randomised controlled trial (RCT) to evaluate the effectiveness of the implementation of A Participative Hazard Identification and Risk Management (APHIRM) toolkit [46], an evidence based, participative, multifactorial intervention for the prevention of WMSDs, to address the work of paramedics employed in an ambulance service. A limited number of tools are currently available to facilitate a comprehensive assessment of physical and psychosocial hazards in the workplace [47], which may be a barrier to achieving the necessary practice change. The APHIRM toolkit was selected as the intervention for this study because it is freely available and was one of three ‘comprehensive’ tools for risk management of WMSDs in workplaces (that addresses both physical and psychosocial hazards) identified in a recent systematic review [47]. Additionally, the APHIRM toolkit uses a participative approach based on principles of implementation science [46]. The effectiveness of the intervention in work groups, in terms of musculoskeletal health (pain and discomfort) and physical and psychosocial hazards will be measured using quantitative data. A process evaluation will document key activities undertaken in the PE process and identify barriers and facilitators, to inform future interventions using the APHIRM toolkit beyond the outlined trial and addressing the previously identified issue of poor description of PE interventions. A rigorous degree of enquiry is important because high quality studies of workplace interventions have been identified as being needed for some time, to expand the implementation evidence available to organisations wishing to address the problem of WSMDs [25, 26, 28, 41, 48, 49] and potentially accelerate evidence uptake in real world settings.

The aims of this study are to:Evaluate the process of implementing the APHIRM toolkit.Evaluate the impact of the implementation of the APHIRM toolkit on the musculoskeletal health and physical and psychosocial risk profile of work groups, 12 months from initial implementation.

To evaluate the impact of the APHIRM toolkit, the following hypotheses will be tested by comparing the results in intervention and control work groups:There will be a significantly greater reduction in self-rated pain and discomfort scores in the intervention work groups compared to the control work groups over a 12-month period.There will be a significantly greater improvement in the level of self-rated exposure to work-related physical hazards in the intervention work groups compared to the control work groups over a 12-month period.There will be a significantly greater improvement in the level of self-rated exposure to work-related psychosocial hazards in the intervention work groups compared to the control work groups over a 12-month period.

## Methods/design

### Participants

The intervention will be conducted in the Queensland Ambulance Service (QAS), Australia. The organisation employs more than 4,000 ambulance officers, including paramedics, who work from more than 300 ambulance response locations [50] across 1,727,000 square kilometres and servicing more than 5.22 million people [51, 52]. The organisation was approached by the lead author, proposing the APHIRM toolkit as an evidence-based risk management intervention designed to comprehensively address WMSDs. Operational factors may influence the implementation of this study protocol. For example, given the key role of paramedics in the COVID-19 global pandemic and the potential impact on personnel, an increase in COVID-19 case numbers may cause delays to recruitment or the variation of indicative timeframes to move through the intervention. Senior leadership are of critical importance in leading the implementation of APHIRM toolkit; hence, a change in senior leadership personnel could also impact the trial.

### Inclusion and exclusion criteria

To practise in Australia, paramedics must be registered with the Paramedicine Board of Australia [53]. In this study, participants must be registered paramedics, employed and assigned by the organisation for their day-to-day work, to either an intervention or a control work group at the time the survey is offered to that work group. Participants may be of any rank and performing regular direct clinical activities with patients e.g., advanced care paramedics; critical care paramedics; operational supervisors; graduate paramedics. Small, specialised groups of paramedics are excluded from the study to enhance the homogeneity of the potential participant cohort, that is, where their job design is significantly different to the included participants e.g., bicycle response paramedics, flight paramedics. Participants on a continuous period of absence from the assigned workplace and duties, expected to be greater than or equal to five weeks at the time they become eligible for the study, will be excluded because completion of the survey requires recall of the current work exposures. The organisation also employs other ambulance officers who are not registered paramedics, and hosts student paramedics during practical clinical placement. These individuals are not registered, so do not meet the inclusion criteria.

### Intervention

The APHIRM toolkit comprises a set of open source, online tools and procedures designed to guide organisations in planning and taking a comprehensive approach to reduce WMSD risk, using the five stages of the risk management cycle [46]. The APHIRM toolkit focuses on managing the WMSD risk in groups of people doing a particular job, with active participation from workers, addressing three key evidence to practice gaps which have been identified, that is, the typically narrow focus on physical hazards; the need to actively involve workers in the risk management process and that risk controls address risk at the source, in accordance with the hierarchy of controls [46]. The key activities involved in the implementation of the toolkit include conducting an online survey, undertaking a participatory risk management process to develop an action plan, implementation of the action plan and repeating the survey to evaluate the outcomes.

The process of implementing the toolkit will be led by a WHS Practitioner (WHSP) facilitator, the lead author, a Certified Professional Ergonomist, with over 20 years’ experience working in health, safety and ergonomics roles, principally in the healthcare sector. To preserve the fidelity of the implementation of the intervention for this trial and account for available resources, a decision was made to use only one WHSP facilitator. This reduces variability in processes but may impact generalisability of the results to situations where a less skilled or experienced WHSP facilitator is implementing the APHIRM toolkit. The WHSP facilitator is a permanent employee of the organisation, which mimics the ‘real-world’ implementation of the APHIRM toolkit. As a result, they are known to the key management personnel and some individual participants in this study. Some practical benefits arise such as trust and confidence through already having established relationships, which may contribute to successful implementation, but may result in over-estimation of the impact. Also due to familiarity, the WHSP facilitator needs to be cognisant of potential bias and influence on participants. The WHSP facilitator will take active steps to manage any potential conflict of interest throughout the study, including ensuring participants are clear that survey participation is voluntary.

### Survey

The survey is the hazard identification and risk assessment component of the risk management processes. The process of developing the survey is fully described by the APHIRM toolkit authors [46] and information demonstrating the validity of the survey is available [54, 55]. Pilot testing during the APHIRM survey development identified that an online survey would facilitate uptake in workplaces and this was achieved through dedicated software development [46]. During the development of the survey, one study involved administering a pilot survey to a large cohort of paramedics [19, 20].

### Information technology

The APHIRM toolkit portal includes automated survey generation, data analysis and reporting modules. An organisational account, managed by the WHSP facilitator, has been initiated in the APHIRM toolkit portal, following the organisation’s approval of the study. The terms of use for the organisational account include that access to content submitted by the organisation is granted to La Trobe University. The APHIRM toolkit portal holds data collected through the surveys and information generated by intervention work groups and their risk management teams (RMTs). Testing of the portal has been undertaken by the WHSP facilitator on organisational devices (mobile and fixed), to ensure that the APHIRM portal works using a mock RMT, which was used to facilitate engagement of senior management. The portal design provides a 24/7 ‘shop front’ for RMT collaboration and documentation, a vital function in this context where reliance on face-to-face collaboration alone could lead to delays. The organisation also has well established virtual team collaboration tools such as shared team sites and video conferencing available for RMTs in this study and all registered paramedics have access to a tablet device with internet access, while on duty.

### Design of the study

A mixed-methods, two-arm (intervention and wait-list control) cluster RCT will be used to evaluate the implementation and the effectiveness of the APHIRM toolkit in work groups of participants, within the organisation. A work group comprises ideally one, or if needed, more than one, ambulance station. Work groups will be referred to hereafter as a ‘control work group’ or an ‘intervention work group’. The cluster design was selected for several reasons. Firstly, the design reflects the usual way in which an organisation implements WHS initiatives. Typically, the manager of a group of workers, in this case, the Officer-In-Charge (OIC) of an ambulance station, leads an initiative under the guidance of a WHS practitioner. Secondly, a cluster design ensures that all eligible participants in the intervention work group are offered the intervention. This avoids contamination between individual participants which would be expected when randomising individual participants within a work group to intervention or control conditions. The participative process—inherent in the APHIRM toolkit design—means that individual participants within a work group are encouraged to discuss the intervention, thus contaminating results. Lastly, mobility of the workforce between ambulance stations is expected. A study design which relied on comparison of individual survey results 12 months later would be impacted by a substantial drop out rate, compromising the utility of the study. The importance of robust design, conduct and reporting of cluster RCTs is recognised; the study will be conducted in accordance with Consolidated Standards of Reporting Trials (CONSORT) guidelines for RCTs [56].

Due to the availability of resources, with only one WHSP to facilitate the study, a rolling recruitment process is planned, with three consecutive time periods. Three intervention work groups and three control work groups will be randomly allocated, in three batches, to each recruitment period which will commence approximately six weeks apart. The six-week timeframe was deemed to be the minimum time for the initiation and sufficient embedding of the required toolkit components in multiple work groups, following which WHSP facilitator time can be directed toward the next allocation of six work groups. This timeframe will be adjusted to meet the operational requirements of the organisation at the time, if required.

A version of the intervention, taking into account the findings of this study, will be offered to wait-list control work groups at the conclusion of the 12 month follow up survey and study. This design ensures that the workforce feels valued, and the organisation meets its duty of care, while balancing the benefits of rigorous study design, providing an appropriate solution to the ethical issue posed by not offering the intervention to all work groups participating in the study.

A Standard Protocol Items: Recommendations for Interventional Trials (SPIRIT) schedule of enrolment, interventions and assessments for this study has been completed (see Supplementary File 1).

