**Fig. 1 Fig1:**
[figure not shown]
Recruitment and randomisation

Work groups will be finalised as close as possible to the commencement of the intervention. The WHSP facilitator and the region’s senior manager will therefore be aware of the identity of all eligible work groups and participants within them. At this time, work groups will be assigned a de-identified code for randomisation. At the agreed commencement of the first recruitment period, a de-identified list of all eligible work groups will be provided to a research assistant not involved with the study, who will randomly assign six work groups in total to the trial (three to the control and three to the intervention arm) using a random number generator in Microsoft Excel. The research assistant will provide the WHSP facilitator with the de-identified work group allocation for the recruitment period. The WHSP facilitator will re-identify the allocated work groups, thus revealing the allocation immediately prior to the commencement of the intervention. The research assistant will repeat this process at the commencement of the second and third recruitment periods until all eligible work groups have been allocated to the trial.

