### Analysis

#### Quantitative analysis

The unit for analysis of the primary and secondary outcomes is a cluster (survey responses from a work group). Analysis will be conducted following CONSORT guidelines for cluster-randomised trials [56]. Means for each of the three variables (pain/discomfort score; exposure to physical hazards score and exposure to psychosocial hazards score), at baseline and 12 month follow up, will be generated for each cluster. The mean change by cluster will be calculated by subtracting the baseline from the 12 month follow up score. Analysis will be conducted treating these as continuous variables [63], using a two-sample test, for example a t-test where *n* = total number of clusters, comparing outcomes for the two arms. Data will be cleaned and examined for normal distribution prior to analysis. Differences in cluster sizes will be identified and accounted for using suitable analysis, which will be reported with the results.

The descriptive data will be presented and used when interpreting the results achieved in the work groups. The information collected from wait-list control and intervention work groups about the usual care activities conducted over the 12-month study period, will also provide useful insight to any differences between groups relevant to the analysis.

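### Work groups are randomised 3:3 within each recruitment period, but the stated two-sample test has no period term, so power may be lost

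*Protocol article*

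**What the plan says.** **Allocation.** Under Design of the study, the protocol article states: "Three intervention work groups and three control work groups will be randomly allocated, in three batches, to each recruitment period". It spaces the starts of the periods by about six weeks, calls this the minimum and allows the spacing to be adjusted for operational needs. Under Recruitment, randomisation and allocation of work groups, a research assistant will "randomly assign six work groups in total to the trial (three to the control and three to the intervention arm"), and then: "The research assistant will repeat this process at the commencement of the second and third recruitment periods". There are thus three separate draws, each fixed at 3:3, giving 18 work groups.

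**Analysis.** Under Quantitative analysis, the analysed quantity is defined as follows: "The mean change by cluster will be calculated by subtracting the baseline from the 12 month follow up score". The arms are then compared "using a two-sample test, for example a t-test where" n is the number of clusters. Unequal cluster size is the only feature the section says will be accounted for; recruitment period is not mentioned. The Qualitative analysis section raises intervention timing only as a possible subject of further analyses prompted by the process evaluation, which leaves the primary test unchanged.

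**The concern.** Recruitment period is a blocking factor by design, and a plain two-sample test treats the 18 work groups as if they had been allocated in one unrestricted draw. Anything that shifts the 12-month change of all six groups in a period cancels from the difference between arms, because each arm has three groups per period. It does not cancel from the variance estimate, which is taken within arm across all three periods.

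Periods could differ in change. The Participants section says a rise in COVID-19 cases may delay recruitment, and Design of the study lets the start dates move. A disturbance around either survey would affect both arms of a batch alike.

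At stake are efficiency and interval width in a trial of 18 clusters whose Discussion already concedes that power for pain/discomfort may be limited.

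**Working it through.** **1. The plan's own figure** (Power and sample size, Table 1: SD 8.3, difference 4, alpha 0.05, power 0.80, ICC 0.05, mean cluster size 18, cluster variation 0.5625).

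- Per arm: 2 × (1.960 + 0.842)² × 8.3² / 4² = 67.6, rounded to 68, so 136 in total. This matches.
- Design effect, reading 0.5625 as the squared coefficient of variation: 1 + ((1 + 0.5625) × 18 − 1) × 0.05 = 2.356. Then 136 × 2.356 = 320, against the stated 317 (1.1% apart).
- 317 × 1.3 = 412. This matches.

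The calculation has no period component.

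**2. Variance of one cluster value.** The documents give no variance for a cluster's change, so I use two assumptions:

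- A: 18 independent respondents at each survey and a stable cluster effect that cancels in the change: 2 × 8.3² × 0.95 / 18 = 7.27.
- B: the protocol's single-survey variance with its design effect: 8.3² × 2.356 / 18 = 9.02.

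**3. What leaving period out does.** Let σ² be the within-period variance of a cluster value and σp² the variance of period effects on change. The true variance of the arm difference is σ² × 2/9, because period cancels. The unblocked pooled variance has expectation σ² + (12/16)σp² = σ² + 0.75σp². At σp = 1.0 the standard error is therefore too large by √(1 + 0.75/7.27) = 1.05 (A) or √(1 + 0.75/9.02) = 1.04 (B). At σp = 1.5 (0.75 × 2.25 = 1.69) the factors are 1.11 and 1.09.

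**4. What including period costs.** Residual degrees of freedom fall from 16 to 14, and the critical t rises from 2.120 to 2.145. With no period effect, the noncentral t gives power of 84.0% unblocked and 83.3% blocked (A), or 75.6% and 74.8% (B).

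**5. Power by assumed period SD** (9 v 9 clusters, difference 4, two-sided 5%; simulated with 200,000 runs per setting, normal cluster values of equal variance). The share is σp²/(σp² + σ²).

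| Variance | Period SD | Share | Unblocked power | Blocked power | Gain (points) | Unblocked type I error |
|---|---|---|---|---|---|---|
| A | 0 | 0% | 84.0% | 83.3% | −0.7 | 5.0% |
| A | 0.5 | 3.3% | 83.3% | 83.3% | 0.0 | 4.8% |
| A | 1.0 | 12.1% | 81.3% | 83.3% | +2.0 | 4.2% |
| A | 1.5 | 23.6% | 77.8% | 83.3% | +5.6 | 3.5% |
| B | 0 | 0% | 75.7% | 74.8% | −0.9 | 5.0% |
| B | 0.5 | 2.7% | 75.0% | 74.8% | −0.2 | 4.8% |
| B | 1.0 | 10.0% | 72.9% | 74.8% | +1.8 | 4.3% |
| B | 1.5 | 20.0% | 69.6% | 74.8% | +5.2 | 3.7% |

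The blocked test holds about 5.0% throughout. Break-even falls at a share of about 3-4%, a period SD of roughly 0.5 to 0.6 points.

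**The case against.** **The analysis is left open.** The article offers the t-test only as an example, says it will follow CONSORT guidance for cluster trials, and is a condensed account. Stratification factors are ordinary analysis-plan content, and an analysis plan that is not shown might add period. This stands in part: the exact test is open. But the class named is a two-sample comparison of two arms with n equal to the number of clusters, which has no place for period. An analysis plan that added it would have to depart from this text.

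**Period effects on change may be small.** If the schedule holds, starts six weeks apart with six-month recall give recall windows overlapping by about 20 of 26 weeks for adjacent periods and 14 of 26 for the first and third. Follow-up at 12 months keeps the season the same, and change scores remove constant period differences. Each batch is drawn at random from the eligible groups of one region. A period SD of 1.5 is also large beside the total between-cluster SD implied by the protocol, 8.3 × √0.05 = 1.86. All of this stands, though longer delays would weaken the overlap argument.

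**Stronger readings to avoid.** A reader might infer that the test is invalid or the estimate biased. Neither follows: balance within period protects the estimate, and the unblocked test errs on the conservative side. A reader might also infer that the periods are known to fall in COVID-19 surges; the text says only that rising case numbers may cause delays. Nor should the single facilitator moving between batches be counted as a simple period effect. Facilitation reaches only intervention groups, so it acts mainly as an arm-by-period interaction, which an additive period term absorbs only partly.

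**Conclusion.** The stated analysis does not match the stated randomisation. The consequence is a possible loss of efficiency, with no threat to validity: the estimate is unbiased, type I error stays at or below 5%, and the harm is over-wide intervals and lower power if periods differ in mean change.

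The size cannot be read from the documents. Across assumed period SDs of 0 to 1.5 points, including period moves power from slightly under one point lower to about five points higher. The result rests on 9 v 9 clusters, a difference of 4 and a cluster-value variance of 7.3 to 9.0. The absolute powers depend on that assumed variance; the contrast between the two analyses depends on it much less. Because the gain may be negligible, the case for the change rests on its very low cost and its agreement with the allocation.

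**What to change.** In Quantitative analysis, state that the cluster-level primary and secondary outcomes will be analysed with a linear model containing arm and recruitment period (three levels, fixed), leaving 14 residual degrees of freedom with 18 clusters. If normality is doubtful and a permutation test is used, permute arm labels only within recruitment period. Whatever method is chosen for unequal cluster sizes should keep the period term. Settle this before outcome data are examined.

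The cost is a change of wording and two degrees of freedom: under one power point for the planned change analysis if periods do not differ. Sample size, conduct and participants are unaffected.
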